### Selection and randomization of CTC

A site assessment will be performed before the final site selection and sites will be selected to participate in the study based on infrastructure feasibility, last numbers of children enrolled into CTC during the past year, numbers and qualification of staff affiliated to CTC and balanced representation of the different level of health facilities and urban versus rural affiliations. Assignment of sites to one of the two study arms will be done by randomization (Fig. 1). Stratification during the randomization process (e.g. rural versus urban) will be considered.

**Figure 1: bpac002-F1:**
[figure not shown]
study design and flow chart.

The study will be open-label whereby the Konga, caretakers, and the children will be aware of the intervention received since neither the outcome assessor nor person receiving the intervention will influence the outcome. The study’s primary outcome is to reduce the viral load <1000 copies/ml.

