### Recruitment

The healthcare workers (i.e. ART nurses) will identify and recruit children with a viral load of >1000 copies/ml and who were aged 2–14 years. Before recruitment, informed consent will be obtained from their caregivers.

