### Plan for the intervention

#### Role of the health worker

The health workers, usually the ART nurses at the selected facility, will identify children with low VLS and link them to the Konga. They will also continue routine care of the child.

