#### Roles of the Konga

We will provide the standard operating procedures (SOPs) to the Kong such that different person will use for the provision of the desired intervention. The SOP will have specific standards adapted from the National HIV care and treatment guidelines, thus the Konga will use the SOP:

To provide enhanced adherence counseling and intensive follow-up. Here, the Konga will routinely visit the client’s house and at every visit they will assess and document:∘ Medication regimen, storage of drugs at home.∘ Doses missed: how often, why, then solve problem with the client.∘ Side effects such as headache, nausea and vomiting, diarrhea, fatigue, sleeping, difficulty, a dry mouth, a rash, dizziness and a pain and client response.∘ Use of other medications, including traditional medicines.∘ Challenges.Follow-up screening for TB and other comorbidities (members of the Konga will visit the children and screen for opportunistic infection and encourage them to visit the health facility for further management); andProvision of psychosocial support by members of the Konga team.

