### Outcome measures

The study will have two outcome measures. The primary measure will be the adherence, this will be measured by using the standard adherence tool (National AIDS Control Program [32]) and loss to follow-up (retention in CTC), which will be compared in both arms. We will measure these metrics at baseline, subsequent follow-up, and the study’s end (i.e. 6 months). The secondary measure will be the viral load, which will be measured at the baseline and subsequently at the 6-month study’s end, comparing both arms.

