#### End of study (6 months)

At the 6-month point, we will collect data from both arms regarding the viral load, weight, and number of missing doses (adherence).

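### The reason given for an open-label design can hold for laboratory viral load but not for adherence, which the Outcome measures section makes primary

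*Protocol article*

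**What the plan says.** The text under Figure 1, in the section on selection and randomization of CTCs, states: "The study will be open-label whereby the Konga, caretakers, and the children will be aware of the intervention received". The reason follows directly: "since neither the outcome assessor nor person receiving the intervention will influence the outcome". The next sentence reads: "The study’s primary outcome is to reduce the viral load <1000 copies/ml".

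The Outcome measures section ranks the outcomes differently: "The primary measure will be the adherence, this will be measured by using the standard adherence tool". Loss to follow-up is part of that primary measure, and viral load is secondary.

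Three further sections describe how adherence arises and is recorded:
- End of study: "we will collect data from both arms regarding the viral load, weight, and number of missing doses (adherence").
- Baseline data: medication adherence is listed among the data obtained from the child.
- Roles of the Konga: enhanced adherence counselling is part of the intervention, and the items assessed and documented at each home visit include "Doses missed: how often, why, then solve problem with the client".

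On recruitment, the Recruitment section says: "The healthcare workers (i.e. ART nurses) will identify and recruit children with a viral load of >1000 copies/ml". The section on the health worker says that the nurses at the selected facility "will identify children with low VLS and link them to the Konga".

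**The concern.** An open-label design needs an outcome whose measurement does not depend on people who know the arm. The article asserts that it has one, without limiting the assertion to a particular outcome. Its own Outcome measures section then makes primary an outcome that appears to rest on what families say about missed doses.

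Only intervention families are asked about missed doses by the people who counsel them on the subject. They may come to give the answer they believe is wanted. The comparison of arms would then mix a real change in pill-taking with a change in reporting, and the analysis could not separate the two. Clustering adjustment and covariate adjustment do not remove such a bias. The risk is that the trial reports a primary effect on adherence where none exists.

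**Working it through.** **The sections side by side.**
1. The justification requires that neither assessor nor recipient can affect the measured outcome.
2. For viral load, the value comes from a laboratory assay classified at 1000 copies/ml. Behaviour changes it, as intended, but knowledge of the arm does not change the reading. The justification is defensible here.
3. For adherence, the end-of-study measure is a count of missed doses, and the baseline section obtains adherence from the child. Caretakers and children know their arm, and one arm receives counselling on exactly this item. The justification fails here.

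**How much it could matter.** The plan gives no figure for reporting bias, so there is none to reproduce. What follows is an illustration.

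Inputs from the Sample size section: 134 children per arm, 10% loss, 10 CTCs per arm, intra-cluster correlation 0.01. Whether 134 per arm delivers the stated power is a separate question that does not bear on this point. The two-sided 5% level is from the analysis section.

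Assumptions not in the documents: adherence is analysed as a yes/no proportion; the true level p is the same in both arms, at 60%, 70% or 80%; the intra-cluster correlation stated for suppression also applies to adherence; and intervention families over-report by b = 5, 10 or 15 points.

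- Analysed per arm: 134 × 0.9 = 120.6, or 12.06 per CTC.
- Design effect: 1 + (12.06 − 1) × 0.01 = 1.11.
- Effective number per arm: n = 120.6 / 1.1106 = 108.6.
- Reported proportion in the intervention arm: q = p + b. Mean of the two arms: p̄ = (p + q)/2.
- SE0 = √[2p̄(1 − p̄)/n] and SE1 = √{[p(1 − p) + q(1 − q)]/n}.
- Probability of a significant result = Φ[(b − 1.96·SE0)/SE1] + Φ[(−b − 1.96·SE0)/SE1].

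Worked case, p = 0.60 and b = 0.10:
- SE0 = √(2 × 0.65 × 0.35/108.6) = 0.0647.
- SE1 = √[(0.24 + 0.21)/108.6] = 0.0644.
- The first term is Φ[(0.10 − 0.1269)/0.0644] = Φ(−0.417) = 0.338. The second is negligible.

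Probability of a significant result when there is no true difference:

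| True adherence, both arms | b = 0 | b = 5 points | b = 10 points | b = 15 points |
|---|---|---|---|---|
| 60% | 5.0% | 11.8% | 33.8% | 65.7% |
| 70% | 5.0% | 13.0% | 39.8% | 75.7% |
| 80% | 5.0% | 16.2% | 54.2% | 92.2% |

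**Recruitment.** Nurses identify and recruit children, and facility nurses also link them to the Konga. A nurse at an intervention site therefore knows the arm when she links a child. Whether she knows it when she recruits depends on whether recruitment comes before or after site allocation. The text does not say, and Figure 1 was not available for this review.

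**The case against.** The strongest reply is that the justification was written with viral load in mind. The sentence after it names viral load as primary. The abstract, the Sample size section and the Dependent variable section treat viral load the same way, and the analysis section also names a viral-load outcome. On that reading the sentence is merely loose, and adherence is a secondary matter. Much of this stands, and it shows which way the conflict should be resolved. It does not rescue the text as written: the justification is not limited to viral load, the Outcome measures section makes adherence primary, and adherence is compared between arms whatever its rank.

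A second reply is that the content of the adherence tool and the person who administers it are not given. A reader might infer that the Konga's visit notes supply the trial's adherence data. The documents do not say so; they describe what the Konga records during care. They do say that adherence is followed in both arms. So reporting by families is a reasonable inference from the baseline and Konga sections, not a stated fact.

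A reader might also infer that the open-label sentence is false for recruitment, or that nurses recruit knowing the arm. Neither is supported. The sentence concerns influence on the outcome and makes no claim about recruitment, and the order of recruitment and allocation is not stated. Eligibility by age and viral load is objective, so any selection would have to come through who is approached and who consents.

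**Conclusion.** The point holds for adherence. The justification is wrong for an outcome that the article itself calls primary, and following the plan as written could give a biased primary result. It remains defensible for laboratory viral load.

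The size is uncertain. Under the assumptions above, the false-positive rate runs from about 12% (5 points of over-reporting, true adherence 60%) to about 92% (15 points, true adherence 80%). No single value in that range should be quoted as the expected one, because neither the true level nor the reporting shift is in the documents. The illustration also treats adherence as yes/no although a count of missed doses is collected, and it does not address the loss-to-follow-up part of the primary measure.

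Differential recruitment is a separate risk that exists only if children are recruited after site allocation is known. It is a point to settle, not a demonstrated fault.

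**What to change.** - In the text under Figure 1, limit the justification to laboratory measurement of viral load.
- In the Outcome measures section, make viral suppression (below 1000 copies/ml at 6 months) the single primary outcome, in line with the abstract, the Sample size section, the text under Figure 1 and the Dependent variable section. Align the analysis section, which currently names a mean difference in viral load.
- Report adherence as secondary. Measure it with the same tool, administered by the CTC, in both arms, and never from Konga visit records. State the reporting-bias caveat beside the result.
- State whether recruitment precedes site allocation. If it follows allocation, list the eligible children from the CTC2 database, for which permission is already being sought, before allocation is revealed. Report the numbers eligible, approached and enrolled by arm.

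The first three changes are mainly wording. The fourth costs one database extract and some flexibility for children identified late.

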### Data collection

#### Baseline data

At the beginning of the study, we will collect baseline data using a checklist. We will collect information from caregivers and their HIV-affected children. From the caregiver, we will collect data, such as social demographic characteristics, age and sex, level of education, income, and marital status. We will collect data, such as age, sex, and clinical characteristics of the children, and also weight, CD4 count, and VLS. Other data collected from the child will include anthropometric measurements, nutrition status, medication adherence, and opportunistic infection status.

#### Follow-up data

We will follow participants monthly in both the intervention and control arms and observe adherence, retention, and opportunistic infections.

#### End of study (6 months)

At the 6-month point, we will collect data from both arms regarding the viral load, weight, and number of missing doses (adherence).

### Measurement of variables

#### Dependent variable

The dependent variable will be the viral load cell count and it will be classified as suppression when the count is <1000 copies/ml and unsuppressed when >1000 copies/ml.

#### Independent variable

The independent variables will be age, weight, adherence, and opportunistic infection (i.e. TB). The caregivers’ social demographic characteristics, age, sex, level of education, income, and marital status will be the independent variables.

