### Sample size calculation and selection

The trial will be conducted in 20 CTC clinics that deliver HIV care and treatment within the four selected districts (10 CTCs will carry out the intervention and 10 CTCs will carry out standard care). We determined the study size from the primary outcome of proportional HIV-positive children with a viral load >1000 copies/ml. According to THIS (2018), 18% of HIV-positive children under the age of 15 years had a viral load >1000 copies/ml; thus, we assumed that value for standard care. Therefore, under a cluster design, the study will need a total sample size of about 268 children (134 in the intervention group and 134 in the control group) to increase the proportion of children with viral suppression from 18% to 30% with 80% power, ata5% significance level, an intra-cluster correlation of 0.01, and 10% expected loss to follow-up. We carried out this power calculation using the Stata™ function “clustersampsi” command (clustersampsi, binomial p1[0.18] p2[0.3]k[20] rho[0.01] alpha[0.05] beta[0.8]).

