### Data processing and analysis

We will enter data into Excel™ software and analyze it using Stata™ software. Descriptive statistics will summarize continuous data, such as the mean, median, standard deviation, and interquartile range. We will use frequencies and percentages to summarize categorical data. Multiple statistical tests and methods will be employed. The univariate analysis will typically utilize Pearson’s chi-squared correlation or Fisher’s exact test, where appropriate. As for the primary outcome (mean difference in the viral load of HIV-positive children with VLS), we will use an independent *t*-test to compare the means of participants in the intervention and control arms. We will develop a multivariable regression model, adjusting for clustering and other confounders for potential confounding. We will use proportions and tests for different proportions as measures of improvement using the difference in difference. All statistical tests will be two-sided and *P* < 0.05 will be considered statistically significant.

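### The covariate list for viral load does not confine adherence and opportunistic infection to baseline values, although the intervention targets both, and it leaves out baseline viral load

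*Protocol article*

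**What the plan says.** All references are to the Protocol article.

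- **Dependent variable:** viral load, classed as suppressed or unsuppressed at 1000 copies/ml.
- **Independent variable:** "The independent variables will be age, weight, adherence, and opportunistic infection (i.e. TB", followed by caregiver characteristics. No measurement time is attached to any of them, and baseline viral load is not among them.
- **Data processing and analysis:** a multivariable regression "adjusting for clustering and other confounders for potential confounding". No other analysis in that section is said to account for clustering. The section also plans a t-test between arms, and tests of proportions "as measures of improvement using the difference in difference".
- **Baseline data:** weight, adherence, opportunistic infection and viral suppression status are collected at entry.
- **Follow-up data:** each month, in both arms, the team will "observe adherence, retention, and opportunistic infections". **End of study** adds viral load, weight and missed doses at 6 months.
- **Outcome measures:** adherence is called the primary measure. Viral load is the secondary one, "which will be measured at the baseline" and again at 6 months.
- **Abstract, Roles of the Konga, Discussion:** adherence counselling and screening for tuberculosis and other comorbidities are parts of the intervention, and better adherence is the stated route to a lower viral load.

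**The concern.** On the protocol's own account adherence has three roles: a target of the intervention, an outcome, and an explanatory variable for viral load. Opportunistic infection has two: a target, and an explanatory variable. A variable that the intervention changes after randomisation is a mediator, not a confounder. Conditioning on it takes out the part of the effect that passes through it. Follow-up infection has a further problem: more active screening in one arm can change how many infections are found there.

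At stake is the one estimate that respects the randomisation by clinic. If the model uses follow-up adherence, a small arm coefficient could mean that the Konga model does not work, or that it works by the intended route and the model has adjusted that route away. The result could not tell these apart.

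A secondary loss is that the most obvious prognostic value, baseline viral load, is measured but not named as a covariate.

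**Working it through.** The plan gives no figure for this point, so there is none to reproduce. The check has four steps.

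**1. Time points.** Age and the caregiver variables raise no difficulty. Adherence and infection exist at baseline and monthly; weight and adherence exist at baseline and 6 months. The list does not say which value is used, so both readings are open. With baseline values the model is sound. With follow-up values it is not a total-effect model.

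**2. Size of the loss if follow-up adherence is used (illustration).**

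From the sample size section: "to increase the proportion of children with viral suppression from 18% to 30% with 80% power", a total effect of 0.30 − 0.18 = 0.12.

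Assumed, not in the documents: good adherence in 35% of controls and 65% of the intervention arm; a share *s* of the effect acting through adherence; adherence measured without error.

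Model: P(suppressed) = b + d·arm + g·adherence, with
- g = s × 0.12 / (0.65 − 0.35)
- b = 0.18 − g × 0.35
- d = (1 − s) × 0.12

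Example, s = 0.5: g = 0.06/0.30 = 0.20; b = 0.18 − 0.07 = 0.11; d = 0.06. Check: the intervention arm gives 0.11 + 0.06 + 0.20 × 0.65 = 0.30.

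The arm coefficient adjusted for adherence is d. A simulation of 400,000 children gave:

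| Share through adherence | d by formula | Adjusted difference, simulated | Adjusted odds ratio, simulated |
|---|---|---|---|
| 25% | 0.09 | 0.089 | 1.65 |
| 50% | 0.06 | 0.058 | 1.41 |
| 75% | 0.03 | 0.030 | 1.21 |
| 100% | 0.00 | 0.001 | 1.01 |

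Without adherence in the model the difference stays at about 0.12, with an odds ratio of (0.30/0.70)/(0.18/0.82) = 1.95.

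To put these sizes in context, take 134 per arm, 10 clinics per arm, "significance level, an intra-cluster correlation of 0.01, and 10% expected loss to follow-up", and "All statistical tests will be two-sided".
- Per arm after loss: 134 × 0.90 = 120.6, taken as 121, or 12.1 per clinic.
- Design effect: 1 + (12.1 − 1) × 0.01 = 1.111.
- Effective n: 121/1.111 = 108.9 per arm.
- Power = Φ{[Δ − 1.96√(2p̄(1−p̄)/n)] / √[(p₁(1−p₁) + p₂(1−p₂))/n]}.

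For true differences of 9, 6 and 3 points from 18%, power is about 36%, 19% and 8%. The same formula gives about 55% for the full 12 points. That shortfall against 80% is a separate matter, and this point does not depend on it.

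**3. Difference in difference.** Eligibility requires more than 1000 copies/ml. If the baseline value is the qualifying one, baseline suppression is 0 in both arms, and (p_I − 0) − (p_C − 0) = p_I − p_C. This is simply the 6-month difference. It is valid, but it makes no use of how high each child's baseline viral load was.

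**4. Gain from baseline viral load.** For a continuous outcome the residual variance is multiplied by 1 − r², where r is the correlation between baseline and 6-month log10 viral load. The documents do not give r.

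| r | Variance factor |
|---|---|
| 0.1 | 0.99 |
| 0.3 | 0.91 |
| 0.5 | 0.75 |

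**The case against.** The strongest reply is that the protocol never says follow-up values will be used. Every variable in the list is collected at baseline, and the caregiver variables appear only there, so a baseline reading of the whole list is natural. The regression sentence does not cite the list; it speaks of confounders, which properly exclude mediators. The t-test and the tests of proportions carry no covariates and still target the total effect. A final covariate set is often left to an analysis plan, and an unadjusted randomised comparison is valid without baseline viral load.

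Most of this stands, and it limits the point in four ways.
- A reader might infer that the model is fixed to adjust for mediators and so removes the effect under test. The documents leave the time point open, baseline adherence and infection are legitimate covariates, and even with follow-up values only the mediated share is lost. Psychosocial support may act by other routes.
- Weight should not be called a mediator on this evidence: no section makes it an intervention target.
- Study arm is absent from the list, but it is surely implied. This is not a defect in itself.
- The difference in difference on suppression does no harm. It only fails to use the baseline viral load.

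The reply does not dispose of the core. The list is stated, not left out. It names a variable that the same article calls a primary outcome and the route to suppression. The uncovariated tests are not said to account for clustering, so they do not replace the regression.

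**Conclusion.** The point holds as an ambiguity that should be closed before analysis, not as a demonstrated error. As written, the plan allows follow-up adherence and infection into the only cluster-adjusted model. If they enter, its arm coefficient is no longer the total effect. The size of the loss is unknown: the 9, 6, 3 and 0 points above follow directly from assumed mediated shares and say nothing about this trial's true share. The article's own emphasis on adherence as the route is the reason not to presume that the share is small.

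The missing baseline viral load is secondary. It causes no bias. The gain in precision from adding it ranges from 1% to 25% of residual variance for r between 0.1 and 0.5, for a continuous outcome, and r is not given.

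**What to change.** State the total-effect model for viral load explicitly:
- study arm, clustering by clinic, and any strata used in randomisation;
- baseline covariates only, with each listed variable marked as its baseline value;
- baseline log10 viral load added to the list.

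Keep follow-up adherence, opportunistic infection and weight out of that model. Analyse follow-up adherence and infection as outcomes by arm, or in a mediation analysis labelled exploratory. For suppression, report the 6-month difference between arms from this model in place of the difference in difference.

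The cost is wording only. The baseline values are already to be collected. The one practical check is that baseline viral load is recorded in copies/ml and not only as suppressed or unsuppressed.
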